#### Completed by the participant

vi) Social Function - was assessed using the Social Function Schedule [30], a widely used self-completed measure of social function with established reliability and validity.

vii) Wellbeing was assessed using the General Well-Being Scale. This 18 item, self-report instrument was originally developed for the US Health and Nutrition Survey, but has subsequently been used in studies of people with schizophrenia and has good psychometric properties [31].

viii) Satisfaction with mental health services - was assessed using the Client Satisfaction Questionnaire, an eight-item measure that has been widely used in previous studies and is sensitive to change [32].

#### Completed by the participants' key worker

ix) Engagement with mental health services was assessed using the four-item Service Engagement Scale [33].

x) Data on occupational and housing status were gathered indicating whether the participant lived in independent or supported accommodation (and the degree of support provided), together with a short description of any paid work, voluntary work or educational/training activities undertaken by the participant during the previous six months.

xi) Any incidents of suicidal behaviour, violence or aggression in the previous year were recorded using a proforma based on the one used by Johnson and colleagues [34].

xii) Global functioning using the Global Assessment of Functioning Scale (GAF) [24]

was rated by the researcher in instances where it was not possible for them to complete a face-to face assessment of the participant. A 'proxy GAF' based on best available information from whatever contact they had had with the participant, key informants and clinicians was made.

Following the collection of all 24-month follow-up data, participants' electronic and written records were examined to obtain details of any period of inpatient treatment received during the previous two years.

### Study procedures

In each centre researchers publicised the study through meetings with staff at local inpatient units, community teams, day centres and residential units. Researchers visited these teams on a regular basis to remind staff about the study and promote recruitment of potential participants. Researchers were assisted in this by clinical studies officers of the UK Mental Health Research Network. Clinical staff were given a copy of an information sheet which summarised the study protocol and helped them identify patients who may be suitable for the study. Researchers met those who had given verbal consent to be approached about the study, assessed eligibility, provided written and verbal information, obtained written consent, and collected baseline data. Participants were then randomised via an independent remote telephone randomisation service using permuted stacked blocks, stratified by site. The block size was randomly assigned between three and six. Each element within the block was randomly assigned to one of the three treatments in proportion to the size of the block.

Participants, their key worker and their general practitioner were notified of allocation status by an independent administrator. The administrator simultaneously informed local art therapists or activity group facilitators of the allocation status of the participant so that arrangements could be made for the participant to receive their allocated intervention while researchers involved in collecting follow-up data remained masked.

Rater 'masking' was maintained by providing specific instructions to participants and their clinical teams not to disclose treatment details. Data are held securely and all personal identifiers removed, with randomisation details held separately and password protected. Data on participants' uptake of the trial interventions was monitored through proforma completed by group facilitators after each group as described above. Thus researchers did not have to record this information from case files as this would have led to unmasking. Participants completing follow-up interviews were offered a £15 honorarium in recognition of their time in completing research interviews and any inconvenience related to their involvement in the study.

### Sample size

The sample size calculation for the study was based on the primary hypothesis: that those referred to group Art Therapy will have improved global functioning at 24 months compared to those referred to attention control treatment or standard care alone. Global functioning had not been assessed in randomised trials of Art Therapy for people with schizophrenia that had been completed when the study was being planned, so data on mean GAF scores and standard deviations were taken from previous trials of Compliance Therapy and Cognitive Therapy for people with schizophrenia. These interventions demonstrate an improvement in GAF scores of between five and 10 points [16,17]. We powered this trial to be able to detect a difference in GAF score of six points.

To detect a mean difference in global functioning of six points on the GAF (SD = 10.0) at 24 months with a two-sided significance level (α) of 5% and power of 80% would require 45 patients in each arm of the trial. In trials of complex interventions there is likely to be clustering of the intervention effect within therapists. In our recent trial of music therapy for people with schizophrenia we observed an intra-class correlation coefficient (ICC) of 0.125 [35]. However we anticipated that group processes may lead to a greater clustering of effects and decided to use an ICC of 0.175 for this trial. With an estimated cluster size of 8 and an ICC of 0.175 the Design Effect for the trial is 2.22 and a sample size of 100 per group was therefore required. A sample of 100 participants in each of the three arms of the trial would be sufficient to detect a difference of 50% in mean costs, at the 5% level of significance and with 80% power. In anticipation of a 20% loss to follow up at 24 months, we planned to randomise 376 participants, 94 at each centre.

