#### Standard care

Standard care involved follow-up from secondary care mental health services, care coordination, pharmacotherapy and the option of referral to other services. No restrictions were imposed on referral to other services apart from arts therapies which participants agreed not to use until the final follow-up assessment had been completed.

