### Statistical analysis

All primary statistical analysis will use the intention-to-treat principle. The statistical package STATA (version 11.0) will be used for all the analyses. The numbers (with percentages) of losses to follow-up at 12, and 24 months after randomisation will be reported and compared between the treatment arms with absolute risk differences (95% Confidence Intervals); any deaths and their causes will be reported separately.

For our main analysis we will impute baseline missing covariates using either mean or regression imputation to increase power and precision of the estimated treatment effect [36]. We will use all available results without imputation of missing outcomes. For the continuous outcomes, differences in mean score between those randomised to each of the three arms of the trial will be examined using analysis of covariance adjusting by 1) site and baseline value of outcome 2) site, baseline value of the outcome, sex and age. The assumption of linearity will be assessed by residual analysis; if necessary bootstrapping techniques will be employed.

Two sensitivity analyses will be conducted to take into account missing data 1) multiple imputation, which assumes data are 'missing at random', and 2) replacement of the missing GAF scores with those from the GAF proxy measure that we collected from participants' key workers.

We anticipate that there will be clustering of outcomes as a result of patients being assigned to groups facilitated by different therapists in different sites. Such clustering violates the assumption that observed outcomes of individuals are independent and can result in increased standard errors [37,38]. To take account of this we will explore separately therapist and site as random effects and finally a three-level model will be fitted, with patients as level one, therapist as second level, and the site as the third level. If our conclusions depend on which model is adopted we will present all results in the principal paper.

In a secondary analysis we will examine the impact of the level of uptake of groups using Complier Average Causal Effect analysis [39]. Instrumental variable methods will be used to model our outcome adjusting for age and sex. Randomisation allocation will be used as an instrumental variable.

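### One design effect is applied to all three arms although standard care has no trial groups: the 80% power is conservative for Art Therapy versus standard care, and the three-level model leaves standard-care patients without a therapist unit

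*Protocol article*

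**What the plan says.** The Sample size section takes a difference of six GAF points ("We powered this trial to be able to detect a difference in GAF score of six points"), an SD of 10.0, and a "two-sided significance level (α) of 5% and power of 80% would require 45 patients in each arm of the trial". It explains the clustering by therapist effects, expects group processes to strengthen them, and "decided to use an ICC of 0.175 for this trial". With a cluster size of 8 it concludes that "the Design Effect for the trial is 2.22 and a sample size of 100 per group was therefore required". The sentence that follows applies 100 to each of the three arms. The primary hypothesis compares Art Therapy with two comparators, the activity group and standard care alone.

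The intervention sections describe Art Therapy and activity as weekly groups planned for up to eight active members. The third arm is different: "Standard care involved follow-up from secondary care mental health services, care coordination, pharmacotherapy and the option of referral to other services".

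The Statistical analysis section names analysis of covariance as the main analysis. To deal with clustering it will explore therapist and site separately as random effects, and then "a three-level model will be fitted, with patients as level one, therapist as second level, and the site as the third level". If conclusions depend on the model, all results will be presented.

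**The concern.** By the article's own reasoning the design effect comes from being treated in a group by a shared therapist. Two of the three arms have that feature and the third does not. A single design effect for the trial, and a single power figure, therefore describe Art Therapy versus activity but not Art Therapy versus standard care, which is also part of the primary hypothesis. A reader weighing a null result against standard care would judge the design by 80% power for six points, when it was more sensitive than that.

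The same gap appears in the analysis. A model with therapist as its second level needs a therapist for each patient, and standard-care patients have none from the trial. Analysts could reasonably code them in different ways, and those codings give different standard errors for a primary comparison.

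**Working it through.** **Inputs (Sample size section).** Difference 6, SD 10, two-sided 5%, power 80%, ICC 0.175, cluster size 8, loss 20%.

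**The plan's own figures.**
- Unadjusted size: 2 × (10 × (1.960 + 0.842) / 6)² = 43.6, so 44 by the normal approximation. The t-test calculation gives 45 (power 80.4%), as stated.
- Design effect: 1 + (8 − 1) × 0.175 = 2.225, written as 2.22.
- Per arm: 45 × 2.22 = 99.9, so 100.
- Total: 300 / 0.8 = 375, and 4 centres × 94 = 376.

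All four figures reproduce.

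**Power by comparison, 100 analysed per arm.** The variance of the difference is SD² × (DE₁/n₁ + DE₂/n₂), and power is Φ(6/SE − 1.96). The total SD is taken as 10 in every arm, with DE = 2.225 in the group arms and 1 in standard care.

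| Comparison | SE | Power | Difference detectable with 80% power |
|---|---|---|---|
| Art Therapy v activity | 10 × √(4.45/100) = 2.11 | Φ(2.844 − 1.96) = 81% | 2.80 × 2.11 = 5.9 |
| Art Therapy v standard care | 10 × √(3.225/100) = 1.80 | Φ(3.341 − 1.96) = 92% | 2.80 × 1.796 = 5.0 |

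Taken alone with equal arms, the second comparison would need 7.849 × 100 × 3.225 / 36 = 70.3, so 71 per arm (73 if scaled from the stated 45: 45 × 3.225 / 2 = 72.6).

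**Sensitivity of the 92%.**
- Residual SD of 10 with the clustering variance added on top in Art Therapy only: the Art Therapy variance is 100 / (1 − 0.175) = 121.2, and SE = √((121.2 × 2.225 + 100) / 100) = 1.92. Power is 88%, and 81 per arm would be needed.
- Equal total SD, but a t reference on 11 to 12 degrees of freedom (12 to 13 Art Therapy groups, an assumption from 100/8): power is about 86 to 87%. On the same footing, with 22 to 24 degrees of freedom, Art Therapy versus activity has about 78%.

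The range for the standard-care comparison is therefore about 86 to 92%, above the stated 80% in every variant.

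**Effect of coding standard care in the three-level model.** This illustration uses the planning ICC of 0.175, total SD 10 and 100 per arm.
- Each standard-care patient unclustered: SE = √(2.225 + 1) = 1.80.
- Standard care given the same clusters of eight: SE = √(2.225 + 2.225) = 2.11, wider by a factor of √(4.45/3.225) = 1.17.
- One pseudo-cluster per site, assuming 25 patients at each of four sites: DE = 1 + 24 × 0.175 = 5.2, and SE = √(2.225 + 5.2) = 2.72, wider by a factor of about 1.5.

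**The case against.** The strongest reply is that nothing has been miscalculated. Every stated figure reproduces. The activity comparison belongs to the primary hypothesis and needs the full 100 per arm, so with similar numbers in each arm it fixes the size of all three. The 80% is then a floor, and the departure from it is in the safe direction. The article also uses 100 in each arm for its cost comparison, which is a separate reason for equal arms. All of this stands.

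On the analysis, the reply is that the article does not say how standard-care patients enter the model. It ties clustering to assignment to facilitated groups, which describes the group arms. The main analysis is analysis of covariance, with the random-effects models added to it, and a full analysis plan exists that is not shown. This also stands in part. A reader might infer that the article gives every standard-care patient a therapist and so widens that confidence interval by a fixed 17%. The text does not support this, because the 17% follows only if standard care is given clusters of eight, and coding each patient as unclustered gives the appropriate standard error within the same model.

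What the reply does not remove is that the article states a level structure with no second-level unit for one of three arms, and a single power figure for two comparisons with different variances. The unseen analysis plan may settle the coding. If it does, a clause in the article is enough.

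**Conclusion.** The point holds as a conservative simplification and an incompletely defined model. The 100 per arm and roughly 80% power are right for Art Therapy versus activity. For Art Therapy versus standard care, power at 100 analysed per arm is about 92% with equal total SD, and about 86 to 92% over the variance and degrees-of-freedom assumptions tried. These figures rest on the planning values (SD 10, ICC 0.175, eight per cluster). The article says more than eight people could be referred to a group, so actual cluster sizes may differ.

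A reader might infer that the trial size is wrong, that the trial is under-powered, or that standard care should have been a smaller arm. The documents support none of these: the more demanding comparison sets the arm size, the simplification understates power, and near-equal allocation was the chosen design.

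The model specification matters more than the power statement. Under the planning ICC, the standard error of a primary comparison could be 1.80, 2.11 or about 2.7 depending on a coding choice the article leaves open.

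**What to change.** In the Sample size section, state that the design effect applies to the Art Therapy and activity arms only and that standard care was kept at a similar size. Give power by comparison with its assumptions: at 100 analysed per arm, about 81% versus activity, and about 92% versus standard care (86 to 92% over the assumptions above), with detectable differences of about 5.9 and 5.0 points.

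In the clustering analysis, specify a partially nested model: a therapist or group random effect in the Art Therapy and activity arms only, standard-care patients unclustered, and residual variance allowed to differ by arm.

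The cost is a few sentences and slightly more model specification. With few therapists, the arm-specific variance estimates may be less stable. No patient numbers, allocation or data collection change.

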### Statistical analysis

All primary statistical analysis will use the intention-to-treat principle. The statistical package STATA (version 11.0) will be used for all the analyses. The numbers (with percentages) of losses to follow-up at 12, and 24 months after randomisation will be reported and compared between the treatment arms with absolute risk differences (95% Confidence Intervals); any deaths and their causes will be reported separately.

For our main analysis we will impute baseline missing covariates using either mean or regression imputation to increase power and precision of the estimated treatment effect [36]. We will use all available results without imputation of missing outcomes. For the continuous outcomes, differences in mean score between those randomised to each of the three arms of the trial will be examined using analysis of covariance adjusting by 1) site and baseline value of outcome 2) site, baseline value of the outcome, sex and age. The assumption of linearity will be assessed by residual analysis; if necessary bootstrapping techniques will be employed.

Two sensitivity analyses will be conducted to take into account missing data 1) multiple imputation, which assumes data are 'missing at random', and 2) replacement of the missing GAF scores with those from the GAF proxy measure that we collected from participants' key workers.

We anticipate that there will be clustering of outcomes as a result of patients being assigned to groups facilitated by different therapists in different sites. Such clustering violates the assumption that observed outcomes of individuals are independent and can result in increased standard errors [37,38]. To take account of this we will explore separately therapist and site as random effects and finally a three-level model will be fitted, with patients as level one, therapist as second level, and the site as the third level. If our conclusions depend on which model is adopted we will present all results in the principal paper.

In a secondary analysis we will examine the impact of the level of uptake of groups using Complier Average Causal Effect analysis [39]. Instrumental variable methods will be used to model our outcome adjusting for age and sex. Randomisation allocation will be used as an instrumental variable.

The health economic evaluation will be conducted from the societal perspective, covering services received and any productivity losses. Differences in mean costs will be analysed using standard parametric t-tests with the validity of results confirmed using bias-corrected, nonparametric bootstrapping (repeat re-sampling) [40]. Despite the skewed nature of cost data, this approach is recommended to enable inferences to be made about the arithmetic mean [41]. In a secondary analysis, cost-effectiveness will be assessed through the calculation of incremental cost-effectiveness ratios [42] and will be explored in terms of global functioning (primary analysis) and quality adjusted life years using the EQ-5 D measure of health-related quality of life. Uncertainty around the cost and effectiveness estimates will be represented by cost-effectiveness acceptability curves [43].

A full Statistical Analysis Plan was developed by the team and ratified by an independent Trial Steering Group prior to data analysis.

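### The main comparison of arms is an ANCOVA with no group or therapist term, and no cluster-adjusted model is named to decide the co-primary outcomes

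*Protocol article*

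**What the plan says.** Under Statistical analysis, the paragraph that begins with the main analysis states that, for continuous outcomes, differences in mean score between the three arms "will be examined using analysis of covariance adjusting by 1) site and baseline value of outcome". A second version adds sex and age. No group or therapist term appears in either.

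A later paragraph of the same section says that outcomes are expected to cluster because patients are assigned to groups run by different therapists at different sites, and that this breaks the independence assumption. The response is: "To take account of this we will explore separately therapist and site as random effects". A three-level model (patient, therapist, site) is then to be fitted. The rule for disagreement is: "If our conclusions depend on which model is adopted we will present all results in the principal paper".

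The Sample size section makes clustering the main driver of trial size: "With an estimated cluster size of 8 and an ICC of 0.175 the Design Effect for the trial is 2.22", so that "a sample size of 100 per group was therefore required".

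**The concern.** The two sections treat clustering differently. The sample size more than doubles the patients per arm on the premise that members of the same group have correlated outcomes. The model described first, in the main-analysis paragraph, assumes that they do not. If the planning premise is right, that model's standard errors are too small and its confidence intervals too narrow.

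The models that could correct this come afterwards, and none has a stated status. The missing-data analyses are labelled as sensitivity analyses and the complier analysis as secondary, but the clustered models carry no label. Nor do they supply an obvious default:

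- A random effect for site alone does not address correlation within a therapy group.
- Standard care alone has no trial group or trial therapist, so the therapist level needs a definition for that arm.

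What is at stake is the confirmatory conclusion on both co-primary outcomes at 24 months. There are two ANCOVAs and three random-effects models. If they disagree, the plan prescribes what to print but not what to conclude.

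**Working it through.** **Inputs, all from the Sample size section.** Difference and spread: "To detect a mean difference in global functioning of six points on the GAF (SD = 10.0) at 24 months". Error rates and unclustered size: "two-sided significance level (α) of 5% and power of 80% would require 45 patients in each arm of the trial". Cluster size m = 8 and ICC = 0.175. Lower ICC, from the team's music therapy trial: "we observed an intra-class correlation coefficient (ICC) of 0.125". ICCs of 0.05 and 0.01 are assumptions, added to show the range.

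**Step 1: reproduce the plan's figures.**
- Unclustered n per arm for 6 points, SD 10: 44 by the normal approximation and 44.6 by the two-sample t-test, so 45.
- Design effect DE = 1 + (8 − 1) × 0.175 = 2.225, given as 2.22.
- 45 × 2.22 = 99.9, so 100 per arm.
- 100 / 0.8 = 125 per arm, or 375 in total; the planned 376 is 4 × 94.

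The sample-size chain is sound.

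**Step 2: variance that the ANCOVA misses.** Let V be the true variance of the arm difference divided by the variance that an independence model reports.
- Art Therapy v activity (both arms in groups): V = DE = 2.225. The true SE is √2.225 = 1.49 times the reported SE.
- Art Therapy v standard care (one arm in groups, equal arm sizes): V = (DE + 1) / 2 = 1.6125. The true SE is √1.6125 = 1.27 times the reported SE.

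**Step 3: type I error of the nominal 5% test**, α = 2 × [1 − Φ(1.96 / √V)]. For example, 1.96 / 1.49 = 1.31 gives 18.9%, and 1.96 / 1.27 = 1.54 gives 12.3%.

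| ICC (m = 8) | DE | v activity | v standard care |
|---|---|---|---|
| 0.175 (planning value) | 2.225 | 18.9% | 12.3% |
| 0.125 (music therapy trial) | 1.875 | 15.2% | 10.2% |
| 0.05 (assumed) | 1.35 | 9.2% | 7.1% |
| 0.01 (assumed) | 1.07 | 5.8% | 5.4% |

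**Step 4: simulation.** The stated ANCOVA (site and baseline) was simulated with 4 sites, 12 groups of 8 in each group arm, 96 unclustered standard-care patients and 5,000 runs per ICC. The ICC applied to the outcome after baseline adjustment. Rejection rates v activity and v standard care were 19.5% and 12.6% at ICC 0.175, 15.5% and 10.4% at 0.125, and 5.5% and 4.9% at zero. These agree with the formula.

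**Step 5: how often the models would disagree.** Take the planning ICC, no true effect, and a clustered test that holds 5%. The ANCOVA would be significant and the clustered test not in about 18.9 − 5.0 = 13.9% of trials v activity and 12.3 − 5.0 = 7.3% v standard care. Disagreement is not a remote case.

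**Step 6: power of a clustered test at 100 per arm.**
- v activity: SE = 10 × √(2 × 2.225 / 100) = 2.11, so power = Φ(6 / 2.11 − 1.96) = 81%.
- v standard care: SE = 10 × √(3.225 / 100) = 1.80, so power is about 92%.

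**The case against.** A reader might infer that the plan ignores clustering and that the trial's false-positive rate is far above 5%. The documents support neither statement.

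- **Clustering is addressed.** The Statistical analysis section says that it is expected, undertakes to fit a three-level model, and requires all results in the principal paper if conclusions depend on the model. A reader of that paper would see the disagreement.
- **The ANCOVA is not explicitly called decisive.** The reference to the main analysis introduces the sentence on imputing baseline covariates, and the ANCOVA follows in the same paragraph. Reading it as the main model is natural but is an inference. The 19% is the error rate of one reported model, not of a trial-level decision.
- **The inflation is conditional.** The value 0.175 was deliberately set above the observed 0.125. The Trial design section reports lower attendance than anticipated, and the outcome is assessed a year after the 12-month offer of groups ends. Both could weaken clustering. On the other side, more than eight people could be referred to one group, which could enlarge nominal clusters.
- **A full SAP exists.** It was ratified before data analysis, is not shown, and may name the decisive model.

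All four points stand, and they limit the finding. They do not remove it. Printing every result is transparent but gives no conclusion when the results conflict. The only ICC values that the article offers are those at which the ANCOVA's error rate is two to four times nominal against the activity groups or standard care. An unseen SAP does not change what the article itself states.

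**Conclusion.** The point holds in a limited form. The article describes its main comparison of arms with a model that is invalid under its own planning assumption, and it names no cluster-adjusted model to settle the co-primary outcomes.

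The size depends on the realised ICC: about 19% and 12% at the planning value, falling to about 9% and 7% at an assumed 0.05. These figures rest on equal arms, clusters of 8, and clustering in the two group arms only. The article gives no separate ICC for PANSS, so applying the same values to that outcome is an assumption. The inflation is therefore not an established property of the trial. What is established is that the decision is left open whenever the models disagree.

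**What to change.** Before unmasked analysis, name one primary model for GAF and for PANSS total at 24 months. It should be a linear mixed model with arm, site and baseline value as fixed effects, and a random effect for group or therapist in the Art Therapy and activity arms only, since standard care has no trial group. Keep both ANCOVAs as sensitivity analyses. Retain the commitment to report all models, but add that the conclusion rests on the primary model. A small-sample correction to the degrees of freedom is reasonable but optional.

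If the ratified SAP already says this, only the protocol text needs to be aligned with it.

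The cost is wording and wider confidence intervals. No new data are needed beyond the link from each patient to a group or therapist, which the planned therapist-level models already require. The 100 per arm was sized for those wider intervals.

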**Method/Design:**

The MATISSE study is a three-arm, parallel group, pragmatic, randomised, controlled trial of referral to group Art Therapy plus standard care, referral to an attention control 'activity' group plus standard care, or standard care alone. Study participants were recruited from inpatient and community-based mental health and social care services at four centres in England and Northern Ireland. Participants were aged over 18 years with a clinical diagnosis of schizophrenia, confirmed by an examination of case notes using operationalised criteria. Participants were then randomised via an independent and remote telephone randomisation service using permuted stacked blocks, stratified by site. Art Therapy and activity groups were made available to participants once a week for up to 12 months. Outcome measures were assessed by researchers masked to allocation status at 12 and 24 months after randomisation. Participants and care givers were aware which arm of the trial participants were allocated to. The primary outcomes for the study are global functioning (measured using the Global Assessment of Functioning scale) and mental health symptoms (measured using the Positive and Negative Syndrome Scale) assessed at 24 months. Secondary outcomes were assessed at 12 and 24 months and comprise levels of group attendance, social function, satisfaction with care, mental wellbeing, and costs.

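### The article states two ways who rated the proxy GAF, and one missing-data sensitivity analysis takes that score at face value although its source may be unmasked

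*Protocol article*

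**What the plan says.** Under Statistical analysis, the main analysis uses the observed outcomes and does not impute missing ones. Two sensitivity analyses for missing data follow. The first is multiple imputation under missing at random. The second is "replacement of the missing GAF scores with those from the GAF proxy measure that we collected from participants' key workers".

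The proxy is described in the Measures section as item xii, under the heading "Completed by the participants' key worker". The text of the item says something else: global functioning "was rated by the researcher in instances where it was not possible for them to complete a face-to face assessment of the participant", and the proxy was "based on best available information from whatever contact they had had with the participant, key informants and clinicians was made".

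On masking, the Abstract (Method/Design) says: "Outcome measures were assessed by researchers masked to allocation status at 12 and 24 months after randomisation". Study procedures says: "Participants, their key worker and their general practitioner were notified of allocation status by an independent administrator". The same section says that masking of raters was kept by "providing specific instructions to participants and their clinical teams not to disclose treatment details".

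**The concern.** GAF is an observer-rated co-primary outcome, so what a score means depends on who gave it and what that person knew. The article gives two answers for the proxy. The analysis section and the Measures heading point to the key worker, who knows the allocation. The text of item xii points to the researcher, who is meant to be masked.

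The analysis then puts the proxy in place of the missing score with no stated allowance for a difference in rating. A rater or informant who knows that a participant was referred to Art Therapy may describe functioning differently from one who knows of no such referral. An error of that kind differs by arm and does not cancel in the comparison. Because this is the only named sensitivity analysis that steps outside missing at random, readers will look to it for reassurance about informative loss. It could agree or disagree with the main result for a reason of measurement rather than of missing data.

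**Working it through.** **1. The statements side by side**

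| Place | Source or rater of the proxy GAF | Knows the allocation? |
|---|---|---|
| Statistical analysis | Collected from key workers | Yes, by Study procedures |
| Measures, heading over item xii | Key worker | Yes, by Study procedures |
| Measures, text of item xii | Researcher, using contact with the participant, informants and clinicians | Researcher masked; informants may know and are told not to disclose |

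The opening of the Measures section says that each measure was completed by the researcher, the participant or the key worker as then indicated, so the headings are meant to identify who completed it. Read literally, the heading and the text of item xii cannot both be right.

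**2. What each reading implies**

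- *Key worker rated.* The substituted scores are unmasked. The Measures section says each measure was taken at baseline, one year and two years, so key-worker scores may also exist for participants who were seen face to face. Some overlap for calibration is then possible.
- *Researcher rated.* The rater is masked, with some exposure to informants who know the allocation. The proxy is made only when no face-to-face assessment was possible, so on this reading there is no overlap at that time point.

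The rater therefore decides both the masking status and whether the proxy can be calibrated against the face-to-face score.

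**3. Inputs for scale**

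The 20% loss and the six-point target come from the Sample size section, whose arithmetic reproduces:

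- Difference 6, SD 10, two-sided 5%, 80% power: 44.6 per arm by the t-test calculation, rounded up to 45.
- Design effect 1 + (8 − 1) × 0.175 = 2.225 (stated as 2.22). 45 × 2.225 = 100.1, or about 100 per arm.
- 300 / (1 − 0.20) = 375; 4 × 94 = 376.

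With 417 recruited (Status of the trial) and equal arms, 417 / 3 = 139 per arm. 20% of 139 is 27.8, so about 28 scores per arm would be replaced.

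**4. Size of the possible shift**

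Let p be the share of scores replaced in each arm and b the difference between arms in mean rating error among the replaced scores. The shift in the arm difference is p × b. With p = 0.20:

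| b (assumed) | Shift, GAF points | Share of six-point target |
|---|---|---|
| 2 | 0.20 × 2 = 0.4 | 7% |
| 5 | 0.20 × 5 = 1.0 | 17% |
| 10 | 0.20 × 10 = 2.0 | 33% |

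For comparison, the unadjusted standard error of an arm difference with 139 per arm is 10 × √(2/139) = 1.20, or 1.20 × √2.22 = 1.79 with the plan's design effect. With clustering, the three shifts are about 0.2, 0.6 and 1.1 standard errors.

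If the replaced shares differ between arms, the shift is p₁b₁ − p₀b₀, where b₁ and b₀ are the mean rating errors in each arm. Even a rating error common to both arms then leaves a residue, so the counts by arm matter.

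**The case against.** The strongest reply is that collecting the proxy from key workers may only mean that they supplied the information, while a masked researcher assigned the score. The text of item xii supports this, and so does the instruction to clinical teams not to disclose treatment. A masked rater using informants under that instruction is not an unmasked rater. This stands as a possible reading. The article does not state it, and the heading over item xii points the other way. Some colouring by informants could remain even so.

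A second reply is that the issue is confined to one sensitivity analysis. This stands in full. A reader might infer that unmasked ratings enter the primary analysis or could overturn its result. They do not, because that analysis uses observed outcomes only.

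A reader might also combine the two accounts and conclude that the proxy is both unmasked and impossible to calibrate. The article does not support that. Lack of overlap follows only from the researcher account, and an unmasked rater only from the key-worker account.

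Third, the size rests on assumed biases. This also stands. The article gives no figure for rating bias, and ten points is a full SD. The calculation further assumes that every missing score has a proxy, although participants who died, for example, may have none, and that every proxy carries the bias. Within each assumed bias, the shift is therefore an upper limit.

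Finally, an analysis plan exists that is not shown, and it may settle the handling of the proxy. It would not remove the conflict between the two statements in this article.

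**Conclusion.** The concern holds in a limited form. The article contradicts itself on who rated the proxy GAF. Followed literally, its analysis section replaces missing scores on a masked outcome with scores from a source told the allocation, at face value. If researchers rated, the weakness is smaller but not absent.

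The reach is one sensitivity analysis, and the main estimate is untouched. The possible shift is at most 0.4 to 2.0 GAF points for an assumed between-arm bias of 2 to 10 points with 20% replaced in each arm. The lower end is negligible beside the standard error. The upper end is a third of the target difference and would matter to a statement of robustness. The documents do not establish that any such bias occurred, or in which direction. The point is worth correcting because the correction is cheap and this is the only named sensitivity analysis outside missing at random.

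**What to change.** - Reconcile item xii, its heading and the Statistical analysis section: state who assigned the proxy score and whether that person was masked. If key workers gave the scores, label the analysis as using unmasked ratings.
- Report the number of proxy scores by arm.
- Repeat the substitution with an arm-specific offset varied over a stated range, and report where, if anywhere, the conclusion changes.
- Where rater and masking status were recorded, also show the result using masked-researcher proxies only. The article does not say whether they were recorded.
- Use the proxy as an auxiliary variable in the multiple imputation only if proxy and face-to-face GAF were both observed in some participants. Without that overlap the data carry no information on how the two relate.

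The cost is a wording correction and one extra sensitivity analysis on existing scores. The primary analysis does not change. The downside is a less clear-cut robustness statement, since a range replaces a single figure.
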